**Assessments**					
PANSS		X			X
MCCB		X			X
FEIT		X			X
TASIT		X			X
UPSA-B		X			X
QoLS		X			X

*SCID 5, Structured Clinical Interview for DSM-5 - Patient version; WAIS-R, Wechsler Adult Intelligence Scale revised; TAU, Treatment as usual; PANSS, positive and negative syndrome scale; MCCB, Matrics consensus cognitive battery; FEIT, facial emotion identification test; TASIT, The Awareness of Social Inference Test; UPSA-B, UCSD Performance-based Skills Assessment; QoLS, Quality of Life Scale.*

### Data Analysis

An assessment of the statistical power of this study was performed using an effect size analysis of the studies included in a meta-analysis (49). The results are very satisfactory: with a statistical power ≥ 0.8 and a significance level of < 0.05, our study needs a total sample of 68 subjects largely below the 80 subjects that will be recruited.

Neuropsychological, psychopathological and cognitive functioning evaluations will be conducted pre and post interventions. Statistical analysis will be conducted by ANOVA for repeated measures, focusing on the role played by different types of interventions in each group regarding the aforementioned domains.

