## Materials and Methods

### Subjects

The study will be carried out at the Department of Psychiatry of the University of Campania “Luigi Vanvitelli” in Naples, and the Department of Mental Health and Addiction Services, ASST Fatebenefratelli Sacco in Milan. Eighty consecutive outpatients with a diagnosis of schizophrenia/schizoaffective disorder according to DSM-5 criteria, confirmed by the Structured Clinical Interview for DSM-5-Patient version (SCID-I-P) will be enrolled, 40 in each center.

Inclusion criteria are: (1) age between 18 and 50 years; (2) clinical stability defined as no major pharmacological treatment modifications in the last 3 months; (3) illness duration < 10 years; (4) at least 5 years of school education. Exclusion criteria are: (1) medical conditions that cause disabilities; (2) a history of alcohol and/or substance abuse.

Subjects will be considered “drop out” when: (1) they do not participate in the study sessions for 3 consecutive weeks, or withdraw the consent to continue the study; (2) they do not participate in the study sessions for 3 consecutive weeks, re-join the program and then accumulate 2 more weeks of absence from the study (in total 5-week interruption of the program, even when non-consecutive); (3) worsening in psychopathological condition requiring a substantial modification of the pharmacological therapy and/or a hospitalization.

Subjects will be randomly assigned to the SoCIAL or the TAU group. Overall, 40 patients (20 for each center) will be assigned to SoCIAL and 40 (20 for each center) to the TAU. Subjects will be evaluated before starting the program and at the end of the intervention.

The study will be approved by the Ethics Committees of the two centers. All enrolled subjects will sign an informed consent form, approved by the Ethics Committees.

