### Randomization

Following eligibility and baseline assessment participants will be randomly assigned to either the intervention or control (TAU) group using an *ad hoc* Excel spreadsheet (69). We will stratify randomization by age, gender and years of education.

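### With one pre and one post value, the group-by-time test of the planned repeated-measures ANOVA is a change-score test; adjusting for the collected baseline is generally more precise at little cost

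*Protocol article*

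**What the plan says.** The Data Analysis section of the protocol article names the method: "Statistical analysis will be conducted by ANOVA for repeated measures, focusing on the role played by different types of interventions in each group". It states that "evaluations will be conducted pre and post interventions", and the Subjects section confirms two occasions only: "Subjects will be evaluated before starting the program and at the end of the intervention". The Limitations section leaves follow-up to future studies.

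The Randomization section puts the baseline assessment ahead of allocation: "Following eligibility and baseline assessment participants will be randomly assigned to either the intervention or control (TAU) group". Stratification is by age, gender and years of education, not by the baseline value of any outcome. Allocation is equal: "40 patients (20 for each center) will be assigned to SoCIAL and 40 (20 for each center) to the TAU". The Treatment as Usual section names the only covariate, recorded therapy hours. Nothing in the article adjusts a post score for its own baseline.

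**The concern.** In a two-arm trial with two occasions, the group-by-time interaction compares the mean change between arms. It uses the baseline by subtracting it in full, which is the same as fixing the regression slope of post on baseline at 1. When the true slope is below 1, subtraction over-corrects and adds baseline noise to the comparison. ANCOVA estimates the slope from the data, targets the same between-arm effect under randomisation, and removes the effect of chance baseline imbalance.

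Precision matters by the article's own reasoning: the Introduction and Limitations both defend a TAU-only control as protection against type II error. An analysis that gives up some power works against that aim.

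**Working it through.** **Inputs from the article.** Two arms, 1:1; two occasions; "with a statistical power ≥ 0.8" and "a significance level of < 0.05" (taken as two-sided, since sidedness is not stated); "our study needs a total sample of 68 subjects largely below the 80 subjects that will be recruited".

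**Inputs not in the article, so assumed.** The pre-post correlation r, from 0.3 to 0.9, and the ratio k of post SD to pre SD (1 unless stated).

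**The article's own figure.** No effect size, SD or correlation is given, so 68 cannot be reproduced forward. Solved backwards, 34 per arm gives 80% power at a standardised difference of 0.68 (normal approximation) or 0.69 (t-test). Below, 0.69 is the difference in mean change divided by the SD of change, so that the planned test has 80% power at 68 by construction.

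**Step 1: the identity.** With two arms and two occasions, the interaction F equals the squared t for change scores. On one generated data set both were 12.1230.

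**Step 2: variances (equal SDs).**
- Change score: 2σ²(1 − r)
- ANCOVA residual: σ²(1 − r²)
- Ratio: (1 − r²) / [2(1 − r)] = (1 + r)/2

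**Step 3: charge ANCOVA its costs.** With n = 34 per arm, the degrees of freedom fall from 66 to 65. Chance imbalance multiplies the variance by 1 + 1/(2n − 4) = 1 + 1/64 = 1.0156.

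**Step 4: power.** The change-score noncentrality is 0.6896 × √(34/2) = 2.84. At r = 0.5, ANCOVA has 2.84/√0.762 = 3.26 on 65 df, which gives 89.4%. Change-score power is 80% at 68 patients and 86.1% at 80 in every row.

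| r | (1+r)/2 | × 1.0156 | ANCOVA power, N = 68 | 68 × (1+r)/2 | ANCOVA power, N = 80 |
|---|---|---|---|---|---|
| 0.3 | 0.65 | 0.660 | 93.2% | 44 | 96.3% |
| 0.5 | 0.75 | 0.762 | 89.4% | 51 | 93.7% |
| 0.7 | 0.85 | 0.863 | 85.4% | 58 | 90.7% |
| 0.8 | 0.90 | 0.914 | 83.4% | 61 | 89.0% |
| 0.9 | 0.95 | 0.965 | 81.4% | 65 | 87.4% |

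The fifth column is the number of patients giving ANCOVA the precision that 68 give the change score, before the costs in Step 3. Simulation with 20,000 trials per setting agreed: change against ANCOVA was 80.2% against 89.3% at r = 0.5, 80.0% against 85.4% at 0.7, and 80.6% against 80.5% at 0.95. Type I error was about 5% for both.

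**Step 5: unequal SDs.** With pre SD 1 and post SD k, the change variance is 1 + k² − 2rk and the ANCOVA variance is k²(1 − r²). Their difference is (1 − rk)², where rk is the regression slope. So before the small costs in Step 3 ANCOVA is never worse, and the gain vanishes as the slope reaches 1. At k = 1.2:
- r = 0.7 (slope 0.84): 0.7344/0.76 = 0.966, against 0.85 with equal SDs
- r = 0.8 (slope 0.96): 0.5184/0.52 = 0.997, against 0.90 with equal SDs

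**Availability of the baseline.** The Randomization section and Table 1 place assessment before allocation. The phase list under Length of the Study mentions randomisation one phase ahead of assessment, and the two should be reconciled. On either reading the baseline precedes the intervention. Table 1 omits the SLOF, but the same phase list schedules real-life functioning before and after treatment.

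**The case against.** The strongest reply is that nothing here is invalid. Under randomisation the change-score test is unbiased and holds its type I error, and a condensed article may leave covariates to a fuller plan. The first part stands: this is a loss of efficiency. The second stands only in part, because the article does not leave the method open. It names repeated-measures ANOVA and one covariate, and therapy hours cannot stand in for the baseline score.

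The size can also be challenged, and fairly. It rests on assumed r, on equal SDs, and on setting the change-score test at 80% for 68 patients. If 68 came instead from a standardised post-score difference of 0.69, the change-score test at r = 0.7 would have 95% power against 97% for ANCOVA; at r = 0.5 it would be 80% against 89%.

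A reader might draw three stronger inferences that the article does not support:
- **Efficacy judged by within-arm pre-post tests.** The closing phrase about interventions in each group is loose. But the Abstract, Introduction, Treatment as Usual section and Conclusion all set a SoCIAL-versus-TAU comparison, and no within-arm efficacy test is planned.
- **The group main effect as the efficacy test.** That term averages pre and post and would halve the effect, but the article nowhere assigns it that role, and the interaction is the natural term.
- **No power to spare.** The article plans 80 patients against 68 needed, a margin of 12.

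**Conclusion.** The point holds as a matter of efficiency, not bias. With two occasions, the planned interaction test is a change-score test, and ANCOVA on the existing baseline is generally more precise. On the stated calibration and equal SDs, the gain at 68 patients is about 9 percentage points of power at r = 0.5, 5 at 0.7, 3 at 0.8 and 1 at 0.9. It is practically nil near r = 0.95, or wherever the slope of post on baseline is close to 1. The direction is secure, apart from a trivial finite-sample cost at very high correlations. The size is conditional, because the article gives neither r nor the SDs. The change is worthwhile, but the trial's validity does not depend on it.

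**What to change.** State in the analysis plan that the efficacy test for each endpoint is an ANCOVA of the post score on arm, the baseline value of that endpoint, the stratification factors (age, gender, years of education) and centre. A baseline-constrained mixed model is an equivalent choice and also keeps patients whose post value is missing. Report the adjusted SoCIAL-minus-TAU difference with its 95% CI.

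No new data are needed. The statistical price is one degree of freedom for the baseline term and about 1.5% variance at 68 patients, plus a few degrees of freedom for the stratification factors and centre.

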## Conclusion

SoCIAL is an individualized rehabilitation intervention, specifically designed to improve SC and metacognitive abilities in patients with schizophrenia or schizoaffective disorder. Therefore, this program is meant to train only SC and metacognition, leaving out the other cognition domains. In the recent literature it is still debated whether a combined intervention (i.e., that trains neurocognition using a cognitive remediation training, CRT, along with SC) (89) is better than SC training, as the combined intervention leads to greater improvements in different cognitive domains and in social cognition than CRT alone, a recent meta-analysis indicates that CRT does not enhance the effects of SC training (53). In our opinion, these results (53, 89) indicate unambiguously that the active ingredient to improve social cognition is SCT. Our program consists of two modules: 1) a module that trains emotion recognition and ToM and 2) a module that trains the narrative abilities, focused on metacognition. The SoCIAL program is the first intervention that trains both SC and narrative abilities in subjects with schizophrenia or schizoaffective disorder. To our knowledge, very few studies investigated the effect of narrative enhancement in this population of patients (64–66). In particular, this program, compared to others, shows some peculiarities in narrative enhancement. Firstly, it will be administered individually (not in a group setting); the individual setting allows the possibility of exploring individual experiences and possible difficulties in understanding one’s own emotions in relation to that experience. Secondly, in different narrative enhancement programs patients are asked to write and share stories regarding their illness. The goal of these interventions is to reduce the self-stigma associated with the disease. In SoCIAL, instead, patients are allowed to pick up a topic of their choice for the narrative enhancement training, including those related to internalized stigma. The goal is to train narrative abilities focusing on developing metacognitive skills in integrating internal experience and mental states with behavior in a coherent narrative. The module is added to transfer therapeutic gains of the SCT to real-life functioning. The SCT and narrative enhancement are expected to potentiate each other in developing emotion recognition and ToM skills and to develop narrative abilities.

Upon completion of data collection, it is expected that participants who receive the SoCIAL intervention vs. the TAU group will improve social cognition, social functioning and quality of life. Lastly, this study aims to evaluate if this intervention could lead to improvements in positive, negative and disorganized symptoms of schizophrenia, together with functional capacity and cognition.

The results of this study will add empirical evidence to the benefits and feasibility of SCT and narrative enhancement in people with schizophrenia-spectrum disorders.

## Limitations

The design of this study should be examined considering some limitations. First, a follow-up evaluation should be added in future studies to address persistence over time of the gain in social cognition and real-life functioning. Second, in our study the efficacy of the SoCIAL intervention is evaluated only vs. TAU. As other trials on SCT efficacy had used an active control (90), the inclusion of a TAU control might be seen as a limitation of the study. However, as we try to prove the efficacy of an innovative intervention integrating SCT with narrative enhancement to further improve the gain in real-life functioning, only a TAU control was included to avoid type II error. If our study will demonstrate an effect on social cognition and real-life functioning, the next step will be a phase 2 trial in a large group of subjects randomized to either SoCIAL or an active control group in which only the SCT component will be provided together with traditional homework tasks, controlling for the number of sessions, individualization of therapy, delivery of therapy fidelity procedures, as well as aspecific factors such as motivation of patients and therapists. This could clarify whether the narrative enhancement module is essential for the transfer of therapeutic gain to real-life functioning.

Lastly, our study used FEIT and TASIT as measures of social cognition, although there is a lack of consensus regarding the use of FEIT for the assessment of emotion recognition. However, the results of the Italian Network for Research on Psychoses studies clearly showed the validity of the test in catching the deficits in social cognition of subjects with schizophrenia (6, 10, 15, 34, 91). We believe that its output, corroborated by the TASIT section of emotion recognitions, shall be considered solid.

Another aspect that could be seen as a limitation of our protocol is the lack of inclusion of a social competence measure which could be improved even if no changes in real-world outcomes are detected. However, no study in our knowledge demonstrated an improvement of social competence by SCT and our own data demonstrated that social cognition impact on real-life functioning is mediated in part by functional capacity, as measured using the UPSA-B, which is included in our protocol. Furthermore, the network analysis by our research group showed that social cognition had no link to an included measure of social competence (6, 92).

## Ethics Statement

The protocol has been approved by the Ethics Committee of the Università degli Studi della Campania “Luigi Vanvitelli” – A.O.U. “Luigi Vanvitelli,” A.O.R.N. “Ospedale dei Colli” and by the Ethics Committee of ASST Fatebenefratelli-Sacco of Milan. Written informed consent was obtained from the individuals for the publication of any images or data included in this article.
